### Type of participants

The sample will be composed of 75 patients with depression. Considering the heterogeneity of this population, the following inclusion criteria will be adopted: (1) diagnosed with major depression (single episode or recurrent episodes) as assessed by the MINI [55]; (2) pharmacological treatment for depression (use of antidepressants); (3) not engaged in regular exercise program (e.g., aerobic and/or strength training) for the 6 months prior to the commencement of experimental period; (4) absence of severe motor impairments, musculoskeletal injury, severe respiratory diseases, acute pulmonary embolism, unstable angina pectoris or severe heart failure, vascular brain disease, severe cardiopulmonary dysfunction, acute myocardial infarction or early phase of rehabilitation (critical aortic stenosis, severe hypertrophic and obstructive cardiomyopathy, untreated malignant arrhythmias, untreated severe hypertension, severe pulmonary hypertension), stroke or neurological disease, symptomatic cardiac malformations (e.g., septal defects, patent ductus arteriosus or valvular stenosis), atrioventricular block grade II or III, left bundle-branch block, or ventricular complex arrhythmias.

### Randomization

After baseline assessments, a blind researcher will classify patients into terciles regarding their MADRS score and number of previous depressive episodes. Subsequently, patients from each tercile will be randomly assigned to the control (C), CAE, or AEMC groups. A one-way ANOVA will test for similar initial values for MADRS scores and number of depressive episodes between groups (*P* > 0.05). The Principal Investigator will be blinded to all of the procedures to perform the randomization and analyses.

### Interventions

Both CAE and AEMC groups will exercise twice a week (on non-consecutive days) for 24 weeks at the Social Service of Commerce – Campo Limpo Unity. Each training session will last for approximately 60 min, with 10 min for warm up, 40 min dedicated to the actual exercise interventions, and 10 min for cool-down, following the American College Sports Medicine guidelines [56]. Training intensity will be maintained between 12 and 14 points of the rating of perceived exertion (RPE), which correspond to ~ 70 to 80% of the maximum heart rate [57]. All of the patients will be instructed to not engage in additional physical exercises throughout the intervention period. Individuals in the C group should not perform any exercise training, maintaining activities of daily living and regular visits to the BHU throughout the experimental period. The CAE group will perform continuous aerobic exercise. The AEMC group will perform aerobic exercises with progressive increases in motor complexity, involving displacements with movements of the limbs in phase, antiphase, and out of phase, usage of unstable bases of support and elements such as balls and discs, one-on-one tasks and changes in the external focus of attention (e.g., obstacles, paths, external rhythm). A room of approximately 10 m by 20 m will be used, where participants will perform a circuit (50 s of exercise and 30 s of rest) composed of 10 stations (each station corresponds to a different high motor complexity exercise). Exercise complexity on each station will be increased on an individual basis, as each patient learns how to perform the proposed motor activities. Exercise intensity will be determined by using the RPE scale. A heart rate monitor (H7 bluetooth, Polar, Kempele, Finland) using the app Polar Team (Polar Team, Polar, Kempele, Finland) will also be used to monitor exercise intensity. At the end of each training session, will also be obtained. The RPE scale is a widely used psycho-physical tool to assess subjective perception of effort during exercise [58]. The RPE scale is a 15-grade scale (6–20) in which exercise-related effort is classified in seven intensities (6–8 very, very light; 9–10 very light; 11–12 fairly light; 13–14 somewhat hard; 15–16 hard; 17–18 very hard; and 19–20 very, very hard) [59].

Together with the RPE, the two-sided scales of affective valence and perception of activation will be used [60]. The affective response will be assessed using the Feeling Scale (FS). FS is a single-item scale of 11 dimensions, ranging from − 5 to + 5, commonly used to measure affective valence (pleasure/displeasure) during exercise [60]. Patients will receive standardized instructions related to the use of FS prior to the exercise session. When explaining the FS, patients should understand that, while performing exercise, it is very common to feel a change in basic affect. Some people feel the exercise as pleasurable while others feel the exercise as unpleasant. Additionally, they will be informed that it is possible for a person to experience varying pleasure and displeasure during the exercise duration [48].

In all physical exercise sessions, four exercise scientists will prescribe and monitor the interventions. Exercise scientists have already completed a 20 h workshop to standardize exercise prescription protocols.

### Mini International Neuropsychiatric Interview (MINI)

The Portuguese version of the 7.0.2 MINI will be used to screen patients for symptoms of major depression. The MINI has a sensitivity and specificity of 95% and 84%, respectively [52]. Questions are phrased to allow only ‘yes’ or ‘no’ answers. The MINI explores all the inclusion and exclusion criteria and chronology of 23 diagnostic categories of the DSM-V and has demonstrated satisfactory reliability [61] for all diagnostic sections (except for the section on psychotic disorders). Specifically for major depression, negative responses in questions A1 (A and B) and A2 (A and B) exclude the possibility of the disease. In the case of affirmative answers to questions A1 or A2, seven additional questions are asked (A3; (A) appetite; (B) trouble sleeping; (C) move more slowly than normal; (D) feel tired; (E) feel worthless or guilty; (F) difficulty concentrating; (G) repeatedly think about death). If five questions are positive (in A1–A3), the patient is diagnosed with major depression. Two more questions are asked (A4 and A5) to check if it is a recurrent episode.

### Outcome measures – primary outcome

The MADRS scale [28] encompasses 10 items that assess apparent and reported sadness, inner tension, sleep and appetite changes, concentration difficulties, slowness, inability to feel, and pessimistic and suicidal thoughts. Nine items are based on the patient’s report and one on the psychiatrist’s observations. The higher the score, the greater the presence of depressive symptoms; scores range from 0 to 60 [62]. The MADRS scale will be applied in the pre- and post-intervention assessments.

### Outcome measures – secondary outcomes

#### Clinical outcomes – cognitive function

The Frontal Assessment Battery [29] is a tool designed to evaluate executive function. This instrument takes approximately 10 min to administer its six items, namely (1) similarities (conceptualization) – explores abstract reasoning by presenting pairs of objects from the same semantic category; (2) lexical fluency (mental flexibility) – assesses self-organization, strategy, and change, generating as many words as possible that start with a given letter; (3) motor series – explores motor programming and planning by carrying out Luria’s series (fist-side palm); (4) conflicting instructions – explores sensitivity to interference, giving the opposite response to that of the examiner; (5) go/no-go – assesses inhibitory control and impulsivity; and (6) prehension behavior – assesses the ability to spontaneously inhibit prehension. A maximum score of 18 is obtained adding the score on each of the six items, which are scored between 0 and 3. Each of the six items assesses cognitive and behavioral domains involved in different neural networks.

The Trail Making Test (sections A and B) was developed in the middle of the last century [30] to evaluate visual tracking, attention, mental flexibility, and motor function [63]; it has been used to evaluate the effect of physical exercise on executive functions [20]. The test is divided into two sections; section A requires the connection in ascending order of 25 numbers within circles arranged randomly on an A4 sheet and section B requires the connection between 12 letters and 13 numbers alternately in alphabetical and ascending order [64]. The test should be performed as fast as possible without lifting the pen or pencil from the paper. The score is obtained as the time (seconds) spent to complete sections A and B. The higher the value on these two sections, the worse the participant’s performance.

The RAVLT was originally developed by Andre Rey [31] and became one of the most used memory assessment tests; it was translated, adapted, and standardized to Portuguese. It consists of two lists of 15 nouns (A and B) and a list of distracting words. List A is read five consecutive times (A1, A2, A3, A4, and A5). Immediately after each reading, the patient must repeat the recollected words. Subsequently, list B is read, and the patient has to repeat the recollected words (B1). After reading list B, the patient should verbalize the remembered words from list A (A6). After a 15-min interval, the patient must identify the words from list A from a list of 30 words (A7).

The Digit Symbol Substitution test [32] consists of filling in as many empty boxes as possible using a symbol that corresponds to a number. Patients have up to 90 s to complete the task. The strategy to solve the Digit Symbol Substitution test requires speed of response, sustained attention, visuospatial skills, and cognitive alternation [65]. The top of the form used to apply the test presents nine symbols with corresponding numbers (1 to 9). The subject must write the numbers corresponding to each symbol each time it is presented (up to 120 situations). Performance is measured by the number of correct answers in a 90 s period, with the score ranging from 0 (worst performance) to 120 points (best performance).

The MoCA [33] was designed to assess cognitive impairment (0 to 30 points) in seven cognitive domains, namely visuospatial and executive function (5 points), appointment (3 points), attention (6 points), language (3 points), abstraction (2 points), late evocation (5 points), and orientation (6 points). Recent evidence suggests that MoCA can also be used as an outcome to determine changes in cognitive function after physical exercise interventions in different populations [66–69].

The Stroop test [34] uses three cards containing 24 stimuli each and a white background. Card A is composed of rectangles printed in green, pink, blue, and brown, randomly arranged. Card B is organized similarly to card A, but with rectangles replaced by the words ‘every’, ‘never’, ‘today’, and ‘all’ printed in capital letters in the four colors mentioned. Card C was also organized similarly to card A, representing the interference card in which the name of the colors (brown, blue, pink, and green) printed and written on each card never matches (e.g., brown word printed in pink, green, or blue). For the first card, participants have to state the colors of the rectangles as quickly as possible. For cards B and C, subjects must state the color of the printed words and not the written words. The criterion score was the time taken to perform the task relative to each card.

#### Hippocampal volume

All scans will be performed using a 3 T Magnetom Verio MRI scanner (Siemens Medical Systems, Erlangen, Germany) using a single channel head coil. High-resolution anatomical images will be recorded in the sagittal plane using a three-dimensional inversion recovery gradient echo sequence (Sequence MPRAGE, gradient mode FAST, magnetic preparation NON-SEL, IR, RF pulse type FAST, excitation NON SEL, TR = 2300 ms, TE = minimum, TI = 900 ms, flip angle 9SEG, bandwidth 240H/PIX, base resolution 192, averages 1, concatenations 1, phase oversampling 0%, FOV phase 100%, FOV read 240–256 mm^2^, slice thickness 1.2 mm, slice per slab (number of slices) 160–170, Filter NONE, parallel acquisition technique (iPAT) OFF, Prescan Normalize ON).

The image processing for volumetric determination will use the NeroQuant system^®^ [35] (CorTechs Labs, Inc., San Diego, CA, USA). CorTechs Labs is an FDA 510(k) cleared and CE marked medical device software that automates the quantification of segmented brain structures from 3D T1 MR images. The resulting brain structure volumes are compared to a healthy population of age- and sex-matched normative reference data, which provides clinicians with a framework to better understand brain structure volumes when assessing patients. Output includes disease-specific volumetric data and color-coded images of brain structures. The 3D T1 MR images are uploaded to the NeuroQuant^®^ software for processing. The images are registered to patient brain space. Brain structures are identified and labeled using CorTechs Labs’ Dynamic Atlas technology. The reports and segmented images are then sent back to the researcher via the PACS system.

#### BDNF level

Blood samples will be used to determine BDNF concentration according to the World Health Organization Guidelines [40] after a 12 h overnight fast. The methodological procedures regarding storage, manipulation, and analysis of blood samples will follow the recommendations of Pareja-Galeano et al. [36]. Blood samples will be collected in tubes without additives and coagulated for 24 h at 4 °C. Samples will then be centrifuged at 1500 rpm for 15 min at 4 °C and the supernatants will be frozen at − 20 °C. The levels of BDNF in all samples will be measured using ELISA kits (Mature BDNF RapidTM ELISA Kit Human, BEK-2211-1P/2P, Biosensis, Australia).

#### Ergometric test

The ergometric test will be performed by a physician with extensive experience. Patients will be instructed to not perform exhaustive physical activities and ingest caffeinated and alcoholic beverages within 48 h prior to the test. Tests will be performed in a controlled temperature environment (21–23 °C). Resting electrocardiogram will be performed with 12-lead monitoring, with a previous 5 min rest period (APEX 200, TEB^®^, São Paulo, Brazil) will be used. An incremental test will be performed up to the tolerance limit using a treadmill (APEX 200). Throughout the test, the electrocardiographic signal will be recorded (APEX 200). The exercise protocol will start at 3.1 km h^− 1^, with progressive increases of the slope by 1 or 1.5% every 60 s, until voluntary exhaustion. The criteria for test interruption will be in accordance with the Guidelines of the Department of Ergonomics of the Brazilian Society of Cardiology [70].

#### Cardiovascular risk

##### Overall cardiovascular score

The Brazilian Cardiovascular Prevention Directive recommends the use of the Global Cardiovascular Score [71] as an indicator of cardiovascular risk. For its calculation, age (ratings of − 9 to 8), total cholesterol (ratings of − 3 to 3), HDL-cholesterol (ratings of − 3 to 5), systolic blood pressure (ratings of − 3 to 3), a diagnosis of diabetes (ratings of 0 to 4), and whether the individual is a smoker (ratings of 0 to 2) are considered. After attributing the values of the respective outcomes, the sum of these results in a single value, which corresponds to cardiovascular risk. This ranges from less than 0 (no risk) to greater than 17 (cardiovascular event risk of 30%). Health professionals receive a booklet with details of such calculation from the Brazilian Ministry of Health [72].

#### Metabolic syndrome

The metabolic syndrome is characterized by the presence of three or more conditions from changes in arterial pressure (systolic pressure ≥ 130 mmHg or diastolic pressure ≥ 85 mmHg), fasting blood glucose (≥ 110 mg/dL), central obesity (abdominal circumference, men > 102 cm and women > 88 cm), dyslipidemia (high LDL-cholesterol, men > 40 mg/dL and women > 50 mg/dL), and triglycerides (> 150 mg/dL) [73].

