**Fig. 1 Fig1:**
[figure not shown]
Template of recommended content for the schedule of enrolment, interventions, and assessments

The primary outcome will be the change in the Montgomery-Åsberg Depression Scale (MADRS) score [28]. Secondary outcomes will be (1) cognitive function, assessed by Frontal Assessment Battery score [29], Trail Making Test A and B score [30], Rey’s Auditory-Verbal Learning Test (RAVLT) score [31], Digit Symbol Substitution Test score [32], Montreal Cognitive Assessment (MoCA) score [33], and Stroop test score [34]); (2) hippocampal volume assessed by magnetic resonance imaging (MRI) [35]; (3) BDNF expression [36]; (4) sleep parameters assessed by Pittsburgh Sleep Quality Index score [37], sleep quality assessment by accelerometry and the Biological Rhythms Interview of Assessment in Neuropsychiatry (BRIAN) score [38]; (5) cardiovascular risk assessed by global cardiovascular score, metabolic syndrome, waist circumference, blood pressure, lipid profile (total cholesterol, HDL cholesterol, LDL cholesterol, triglycerides), and glycemia [39, 40]; (6) suicidal ideation and behavior assessed by the Scale Columbia of Suicide score [41] and Scale of Hopelessness score [42]); (7) functionality assessed by gait linear spatial variables [43, 44], Timed Up and Go test (TUG) score [45], TUG cognitive score [46], handgrip strength [47], 6-min walk test [48] physical activity levels (sedentary time, active time, time spent in different physical activity intensities, energy expenditure, and number of steps per day), body weight, and hip and waist circumference [49]; and (8) treatment costs including laboratory procedures, medicines, and doctor consultations per patient [50].

The study will be conducted in accordance with theDeclaration of Helsinki revised in 2008 [51] and approved by the ethics committees of the Department of Health of the city of São Paulo and of the Hospital Israelita Albert Einstein, Certificate of Ethical Appreciation Presentation (PCEA) number 64888017.3.0000.0086. Trial registration is RBR-9zgxzd.

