### Setting

Patients with depression will be recruited in the southern region of the São Paulo city at the Basic Health Unit (BHU; i.e., Arariba Park) in the state of São Paulo, Brazil. This BHU is part of the Brazilian Unified National Health System. First, patients will be referred by the physician team of the BHU if they fulfil the criteria of being 40 years and older, being treated for depression, and have no absolute contraindication to perform physical exercise. After the initial screening, patients will be fully informed of the procedures involved in the present trial and invited to sign an informed consent form. Participants will visit the laboratory on six occasions to perform the following assessments (Fig. 2):Visit 1: Consent form and anamnesis, Mini International Neuropsychiatric Interview (MINI) [52], and MADRS scale [28]. The number of depressive episodes in life and medicine dosage in the last 3 months (necessary clinical adjustments) [53] will be assessed by a trained psychiatrist researcher. Patients diagnosed with depression (single episode or recurrent episodes) will be referred to Visit 2. Patients will be informed that they may terminate their participation in this trial at any time, regardless of the reason.Visit 2: Questionnaire of cognitive function, suicidal ideation and behavior, hopelessness, and sleep quality.Visit 3: Blood samples after a 12 h fasting, functional tests, and instructions to use the accelerometer (GT9X ActiGraph accelerometer, Pensacola, USA) to assess sleep quality.Visit 4: these visits will be used to estimate the typical error of the functional tests (TUG test, TUG cognitive test, handgrip strength, 6-min walk test, body weight, hip and waist circumference); an interval of 48 h will be granted between Visits 3 and 4.Visit 5: Ergometric test and presence of absolute contraindications to exercise.Visit 6: MRI of the brain and instructions to use the accelerometer (GT9X ActiGraph accelerometer, Pensacola, USA) to assess physical activity level.

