#### Blood pressure and heart rate variability

Blood pressure and heart rate variability will be obtained in the supine position after 10 min of rest by an evaluator blinded to other assessments and group allocation. Brachial auscultatory blood pressure will be measured in triplicate on both arms using a sphygmomanometer and a stethoscope (BIC, Standard, Brazil) considering phases I and V of the Korotkoff sounds for the identification of systolic and diastolic blood pressures, respectively. The mean of three measured values, with at least 4 mmHg of difference between them on each arm, will be calculated. The mean value obtained on the arm with the higher blood pressure will be considered for the analysis [74].

For the determination of resting heart rate variability, RR intervals will be obtained by a heart rate monitor (POLAR – V800, USA) for 10 min. The evaluator will visually inspect all RR intervals and correct, via interpolation, any inappropriate or premature RR interval. Any RR interval with a difference greater than 20% of adjacent intervals will be filtered using a moving average algorithm. Normalized RR intervals will be transferred to a dedicated heart rate variability software package (Kubios HRV v 2.1, University of Eastern Finland, Finland) for further analysis. Using the recommendations of the Task Force for heart rate variability, the time-domain (SDNN, RMSSD, and pNN50) and frequency-domain parameters (low frequency, high frequency, and ratio between low and high frequency) will be analyzed and a non-linear analysis (SD1 and SD2) will be performed as previously described [75].

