#### Blood sample collection

All fasting blood samples will be collected in additive-free tubes (serum), in K3-EDTA containing tubes (plasma), and in clot activation gel tubes (whole blood). Whole blood will be frozen immediately after collection of blood samples and stored at − 20 °C. The serum and plasma samples will be centrifuged at 3000 rpm for 15 min at 4 °C. Supernatants will be frozen and stored at − 20 °C until analysis. These samples will be analyzed for lipid profile (total cholesterol, HDL, LDL, triglycerides) and blood glucose levels (Ultrospec 6300 Pro), according to World Health Organization Guidelines [40] and the manufacturer’s instructions.

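### Two cardiovascular secondary-outcome rules are wrong as written: an LDL cut-off that nearly every adult exceeds in the metabolic syndrome definition, and a blood pressure rule that requires readings to disagree

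*Protocol article*

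**What the plan says.** The outcome list under Study design (after Fig. 1) includes "cardiovascular risk assessed by global cardiovascular score, metabolic syndrome, waist circumference, blood pressure, lipid profile" among the secondary outcomes.

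**Metabolic syndrome.** "The metabolic syndrome is characterized by the presence of three or more conditions". The five conditions are raised blood pressure, raised fasting glucose, central obesity, a cholesterol condition and raised triglycerides. The cholesterol condition is "dyslipidemia (high LDL-cholesterol, men > 40 mg/dL and women > 50 mg/dL"). The definition is cited to reference 73. HDL appears in no component, although Blood sample collection states: "These samples will be analyzed for lipid profile (total cholesterol, HDL, LDL, triglycerides").

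**Blood pressure.** The section on blood pressure and heart rate variability states: "The mean of three measured values, with at least 4 mmHg of difference between them on each arm, will be calculated". The arm with the higher mean is then used, citing reference 74. Nothing is said about triplicates that do not meet the rule. Systolic pressure also enters the global cardiovascular score, with "systolic blood pressure (ratings of − 3 to 3").

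No other section corrects either rule.

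**The concern.** A component of a diagnostic count is useful only if some patients meet it and others do not. LDL above 40 or 50 mg/dL hardly separates patients, so it adds one condition to almost everyone's count. The pattern of the cut-offs also suggests a slip: they are sex-specific and higher in women, and the one lipid fraction that is measured but missing from the definition is HDL.

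The blood pressure rule has a similar problem. Repeat readings are averaged for precision and checked for agreement. A rule that asks for a *minimum* difference rejects closely agreeing triplicates and keeps discordant ones.

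At stake are the validity and sensitivity of one derived yes/no outcome, and whether assessors can apply the blood pressure procedure consistently.

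**Working it through.** The plan gives no figure for either rule, so there is nothing to reproduce. The checks below size the effect. All distributions and prevalences are assumptions, because the documents give none.

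**1. Share meeting the LDL condition.** Referred patients are "being 40 years and older, being treated for depression" (Setting). Assume normally distributed LDL with mean 90 to 130 and SD 25 to 40 mg/dL. The share above cut-off *c* is 1 − Φ((*c* − mean)/SD).

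| Mean, SD (mg/dL) | Men, > 40 | Women, > 50 |
|---|---|---|
| 90, 40 (least favourable) | 89.4% | 84.1% |
| 100, 35 | 95.7% | 92.3% |
| 115, 30 | 99.4% | 98.5% |
| 130, 25 (most favourable) | 100.0% | 99.9% |

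The range is about 84 to 100%.

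**2. Effect on prevalence, independent components.** Let *q* be the probability of meeting the cholesterol condition. Then

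P(at least 3 of 5) = P(at least 3 of the other 4) + *q* × P(exactly 2 of the other 4).

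As *q* approaches 1 this becomes P(at least 2 of the other 4).

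- *Lower set*: other four at 0.40, 0.15, 0.40, 0.30. P(at least 3 of 4) = 0.0864 and P(exactly 2 of 4) = 0.2842.
  - Low-HDL condition met by 30%: 0.0864 + 0.30 × 0.2842 = 0.172.
  - LDL condition met by 98%: 0.0864 + 0.98 × 0.2842 = 0.365. Ratio 0.365/0.172 = 2.1.
- *Higher set*: other four at 0.60, 0.30, 0.60, 0.40. P(at least 3 of 4) = 0.2664 and P(exactly 2 of 4) = 0.3912.
  - Low-HDL condition met by 40%: 0.2664 + 0.40 × 0.3912 = 0.423.
  - LDL condition met by 98%: 0.2664 + 0.98 × 0.3912 = 0.650. Ratio 0.650/0.423 = 1.5.

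At the lowest share from step 1 (*q* = 0.84) the prevalences as written are 0.325 and 0.595, with ratios of 1.9 and 1.4.

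The ratio moves with the assumed prevalences. With the other four all at 30%, 95% meeting the LDL condition gives 34%, against 16% if the condition were met by 30%. With all four at 20% the figures are 17% and 7%.

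**3. Effect on prevalence, clustered components.** Components of a syndrome tend to occur together. With a latent correlation of 0.3 to 0.5 among the four others and low HDL, and the prevalences of step 2, simulated ratios fall to about 1.3 to 1.6 at *q* = 0.98 and 1.2 to 1.4 at *q* = 0.84.

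**4. Blood pressure rule.** Assume three independent normal readings. The text does not say whether every pair or only the range must reach 4 mmHg. Simulated share of triplicates that qualify:

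| Within-occasion SD (mmHg) | Every pair ≥ 4 | Range ≥ 4 |
|---|---|---|
| 2 | 0.2% | 33% |
| 3 | 3% | 61% |
| 5 | 17% | 84% |
| 8 | 37% | 93% |

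Under either reading, the triplicates that fail are those that agree best.

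**5. Cost of simply reversing the rule.** At an SD of 3 mmHg, 61% of triplicates have a range above 4 mmHg. With two arms, assumed independent, the chance that at least one exceeds it is 1 − 0.39² = 0.85.

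**The case against.** The case against making much of this is substantial, and most of it stands.

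- **Wording slips.** Both look typographical, in a condensed article that cites its definitions, and the cited sources are not at hand. That the rules are inverted is therefore an inference. This stands. It does not rescue the text, which gives operative thresholds that fail if followed.
- **Spread of the LDL error.** A reader might infer that it runs through the whole cardiovascular-risk domain. It does not. The global cardiovascular score uses total cholesterol and HDL, not LDL, so the error stops at the metabolic syndrome variable.
- **Loss of HDL information.** A reader might infer that an HDL effect would go unseen. It would not: HDL is an outcome in its own right, the lipid profile is named for modelling under Data analysis and power calculations, and HDL is scored in the global cardiovascular score.
- **Loss of blood pressure precision.** A reader might infer that the rule inflates measurement error. With normal errors it does not: at an SD of 3 mmHg the error variance of the mean is about 3.0 whether the range is at least or at most 4 mmHg. A difference appears only under an assumed outlier model, for which the documents give no basis.
- **Bias between groups.** The same rules apply to all groups at both time points, so neither creates a systematic difference between them.
- **Size of the inflation.** The 1.5 to 2.1 figure rests on independence and assumed prevalences; clustering lowers it. This stands.

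**Conclusion.** The point holds in limited form, for secondary outcomes only.

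The LDL condition is nearly constant over the whole range of distributions tried. Metabolic syndrome is therefore overcounted in all groups at both time points, by about 1.5 to 2.1 times under independence with 98% meeting the condition, and by less under clustering or a lower share. That the condition does not discriminate does not depend on what was meant. That low HDL was meant is a reasonable reading of the sex-specific cut-offs and of HDL's absence from the definition, but it needs confirmation from reference 73.

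The blood pressure rule, read literally, excludes agreeing readings and appears to mean *at most*. Blood pressure also enters the metabolic syndrome definition and the global cardiovascular score, but the documents support no numerical estimate of harm. This part is a wording correction plus a missing instruction for triplicates that fail the rule.

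MADRS, the sample size and between-group comparability are unaffected.

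**What to change.** 1. **Metabolic syndrome.** Reconcile the cholesterol condition with the definition in reference 73. It appears to mean HDL-cholesterol below 40 mg/dL in men or below 50 mg/dL in women. Once confirmed, derive the outcome that way at baseline and follow-up. The cost is one phrase, since HDL is already measured.
2. **Blood pressure.** Reconcile the 4 mmHg wording with reference 74 so that agreeing readings are not excluded. Say whether the limit applies to the range or to every pair, and state how discordant triplicates are handled. The cost depends on that choice. A strict 4 mmHg cap with mandatory repeats would, at an error SD of 3 mmHg, call for a repeat in about 85% of patients at each assessment, so the workload should be weighed before such a cap is adopted.

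Trial status reports that no participants had been included, so at that point both corrections could precede all data collection.
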